### Study endpoints

The primary clinical endpoint is the proportion of patients with treatment failure during the trial period, defined as either death, development of end-stage renal disease, major renal or extrarenal flare, sustained doubling of serum creatinine, clinical or renal non-response, requiring induction therapy or plasmapheresis, requiring a dose reduction or discontinuation of mycophenolate—other than established by protocol—for more than 14 or 7 days respectively, discontinuation of belimumab for more than three consecutive doses, inability to complete two rituximab administrations, withdrawal for any reason, or loss to follow-up.

Secondary clinical endpoints will be evaluated at 28 and 104 weeks. Clinical response is defined as a reduction in SLEDAI of ≥ 4 points and no worsening of Physician Global Assessment (PGA) score of > 0.3 points on a scale of 0–3. Other secondary endpoints are clinical remission (defined as meeting the criteria of clinical response and additionally achieving to taper steroids to ≤ 5 mg/day), renal response (complete renal response being < 0,75gr proteinuria per 24 h and a serum creatinine within 125% of baseline), low-level disease activity (SLEDAI ≤ 4 with no activity in major organ systems, hemolytic anemia or gastrointestinal activity and no new disease, PGA ≤ 1 and ≤ 7.5mg prednisolone equivalent), and disease control (SLEDAI ≤ 2 with ≤ 5mg steroids per day) [36]. Patient-reported outcome measure includes the SF-36 Quality of Life questionnaire [37]. Other clinical secondary endpoints are feasibility and safety of combination treatment by monitoring the occurrence of adverse events, with special attention to infections.

The main immunological endpoint is reduction of anti-dsDNA and other disease-specific autoantibodies at 28 weeks, which is also assessed at 104 weeks. Secondary immunological endpoints are reduction of relevant autoantibodies, sustained B cell depletion, and regression of immune complex-mediated excessive NET production at 28 and 104 weeks.

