## Abstract

**Background:**

Belimumab, an anti-B-cell activating factor antibody, is approved for the treatment of auto-antibody positive systemic lupus erythematosus with a high degree of disease activity. Anti-CD20 B cell depletion with rituximab is used in refractory SLE as well, although with variable responses. We hypothesized that incomplete B cell depletion, related to a surge in BAFF levels following rituximab treatment, can cause ongoing disease activity and flares. The Synbiose 1 study primarily focused on immunological effects and shows the preliminary clinical benefit of combined rituximab and belimumab in SLE. The Synbiose 2 study will evaluate the clinical efficacy of combining belimumab with rituximab in patients with severe SLE, allowing the tapering of prednisolone and mycophenolate.

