### Study treatments

All patients will be given standard of care consisting of 3 pulses of 500 mg (< 60 kg) or 1000mg (> 60 kg) of intravenous methylprednisolone. This will be followed by tapered oral prednisolone at a starting dose of 60mg daily together with mycophenolate at a starting dose of 500mg twice daily and increased weekly, titrated to achieve a target AUC of 60-90mg*h/L, with a maximum dose of 4000mg per day. In cases where therapeutic drug monitoring (TDM) is not possible, mycophenolate dose will be titrated against leukocyte counts and tolerability of the patient. Patients randomized to the intervention group will receive standard of care combined with self-administered subcutaneous belimumab 200mg weekly, and two doses of 1000-mg intravenous rituximab 4 and 6 weeks after belimumab initiation. One hundred-milligram intravenous methylprednisolone, 2-mg intravenous clemastine, and 1000-mg oral acetaminophen will be administered prior to rituximab infusions.

In both treatment groups, oral prednisolone will be tapered to 7.5mg before week 28 and to 5mg before week 52 and will be continued at a low dose for the remaining study period. Dose reduction to zero can be personalized to the tolerance of the patient, judged by the treating physician. In the control group, mycophenolate will be reduced by 50% at week 28 and continued for the remainder of the study period. In the intervention group, mycophenolate dose will be reduced by 50% at week 16 and discontinued at week 28. Belimumab will be continued throughout the entire study period. Consequently, after week 28, patients will enter the maintenance phase where they will receive either prednisolone and mycophenolate (control group) or prednisolone and belimumab (intervention group) (Fig. 1). Patients will be monitored closely during the study, with laboratory evaluation and study visits every 2 weeks during the first 8 weeks after inclusion, and increasingly longer intervals during the remainder of the study, up to 2 months eventually. An overview of study visits and assessments per visit is summarized in Table 2.

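### The primary failure composite does not score prednisolone held above the protocol's own taper, so unequal off-taper steroid could move the open-label primary result unseen

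*Protocol article*

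**What the plan says.** Under Study endpoints, "The primary clinical endpoint is the proportion of patients with treatment failure during the trial period". The components are then listed in full. They include "sustained doubling of serum creatinine, clinical or renal non-response, requiring induction therapy or plasmapheresis, requiring a dose reduction or discontinuation of mycophenolate", with limits of 14 days for an unscheduled mycophenolate reduction and 7 days for a discontinuation. The list ends with "discontinuation of belimumab for more than three consecutive doses, inability to complete two rituximab administrations, withdrawal for any reason, or loss to follow-up". No component concerns prednisolone dose, a missed taper or a steroid increase.

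Under Study treatments, the taper is written as a rule for both arms: "In both treatment groups, oral prednisolone will be tapered to 7.5mg before week 28 and to 5mg before week 52". The one sentence on discretion concerns going lower: "Dose reduction to zero can be personalized to the tolerance of the patient, judged by the treating physician".

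Clinical response contains no steroid limit: "Clinical response is defined as a reduction in SLEDAI of ≥ 4 points and no worsening of Physician Global Assessment (PGA) score". Steroid limits appear only in three secondary endpoints (clinical remission, low-level disease activity, disease control), evaluated at weeks 28 and 104. Statistical analysis adds a Mann-Whitney comparison of immunosuppressant dosages.

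The abstract gives the purpose as evaluating the combination while "allowing the tapering of prednisolone and mycophenolate". The Discussion names reduction of cumulative steroid dose without a flare as an aim, and says the combination may be supported even if efficacy is only equal. Strengths and limitations names the open-label design as a limitation.

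**The concern.** The composite treats the study drugs unevenly. An off-protocol mycophenolate reduction of 15 days is a failure. Prednisolone above both milestones through week 104 is not, provided nothing else on the list occurs. Yet prednisolone is the one drug that both arms carry into the maintenance phase.

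Steroid is part of the protocol's own treatment of active disease, and flare and non-response are primary components. Extra prednisolone can therefore prevent a primary event without being counted. Because the planned taper is the same in both arms, any between-arm difference above it is a departure from plan and not part of the randomised contrast. Those who manage treatment know the allocation, so nothing in the design ensures that such departures balance.

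Two conclusions are at stake. A difference in failures could partly reflect unequal steroid. A finding of equal efficacy, which the Discussion says could support the combination, could arise because extra steroid in the worse arm closed the gap.

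**Working it through.** **1. The plan's own figure.** Inputs from Sample size calculation: failure 54% v 23% over 104 weeks, alpha 5%, power 80%, 35 per arm.

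- Hazard ratio = ln(1 − 0.54)/ln(1 − 0.23) = 2.97, as stated.
- Schoenfeld events, two-sided: 4 × (1.960 + 0.842)²/(ln 2.971)² = 26.5, so 27.
- Mean failure rate = (0.54 + 0.23)/2 = 0.385, and 27/0.385 = 70.1. The planned 70 is reproduced.
- Expected failures: 35 × 0.54 = 18.9 in control and 35 × 0.23 = 8.05 in intervention, 26.95 in all. Power = Φ(½√26.95 × ln 2.971 − 1.96) = 80.7%.

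The sample size is sound on its own inputs. It also shows that the primary test rests on about 27 events, so a few uncounted ones matter.

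**2. No true difference, failures averted in one arm only.** Both arms exponential with 54% failing by week 104, 35 per arm. In one arm a random share s of failures is removed and those patients are censored at week 104. The table gives the chance that the log-rank test at two-sided 5% favours that arm.

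| s (assumed) | Rate in that arm | Simulated | Schoenfeld approximation |
|---|---|---|---|
| 0 | 54.0% | 2.5% | 2.5% |
| 10% | 48.6% | 6% | 7% |
| 20% | 43.2% | 14% | 15% |

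The approximation for s = 20%: HR = ln(0.46)/ln(0.568) = 1.37; events = 35 × (0.54 + 0.432) = 34.0; 1 − Φ(1.96 − ½√34.0 × ln 1.373) = 15%. A share of 20% is 0.2 × 18.9 = about 4 patients.

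**3. The other direction.** Planned effect present, failures averted in control only:

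- 10%: control rate 48.6%, HR 2.55, 25.06 events, power 65%.
- 20%: control rate 43.2%, HR 2.16, 23.17 events, power 46%.

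**4. Effect of counting off-taper prednisolone as failure.** Let q be the assumed share of otherwise successful patients above the taper. The new rate is p + (1 − p)q.

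| q control / intervention | Rates | HR | Power at 70 |
|---|---|---|---|
| 10% / 10% | 58.6% v 30.7% | 2.41 | 69% |
| 20% / 20% | 63.2% v 38.4% | 2.06 | 58% |
| 20% / 10% | 63.2% v 30.7% | 2.73 | 82% |
| 10% / 20% | 58.6% v 38.4% | 1.82 | 42% |

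The document gives neither s nor q. These are ranges, not estimates.

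**The case against.** **Existing components catch part of the escalation.** A patient needing much more steroid may meet major flare, non-response, re-induction or withdrawal, and a control patient who crosses over counts as failed. The article does not define a major flare, and the full protocol may do so. This stands. One might infer that every steroid increase escapes the endpoint, but the text does not show that. The gap is steroid above the taper with no other component met.

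**The protocol does not permit holding patients above the taper.** This stands. The discretion sentence might be read as giving the physician free control of prednisolone, but it covers only reduction to zero. Influence over doses above the milestones is an inference from open-label care.

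**Steroid exposure is examined elsewhere.** The secondary endpoints and the dosage comparison are real safeguards and may expose an imbalance. Neither shows whether the primary result would change.

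**The size is hypothetical and generous.** This stands in part. The simulation removes a share of all failures, but many components (loss to follow-up, incomplete rituximab, belimumab interruption) would not plausibly respond to steroid. If half of failures were steroid-sensitive, a further assumption, averting 40% of those would be needed to reach s = 20%. Larger values of s are therefore hard to defend.

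**Keeping steroid goals out of the primary is a legitimate choice, and an averted flare is not a failure.** This is fair for the primary definition: the primary objective is fewer treatment failures, not steroid sparing. It does not meet the need to interpret the result once tapering or equal efficacy is claimed.

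**Conclusion.** The point holds in a limited form. The composite is fixed in the article down to day limits, so the missing prednisolone item is a feature of the definition and not a detail left to another document. Off-taper prednisolone short of the listed events is counted as success, and an imbalance could push the primary result either way. If 10–20% of failures were averted in one arm only, with no true difference and 54% failing in each arm, the chance of a significant result for that arm rises from 2.5% to about 6–14%. Under the planned effect, the same shares averted in control only would lower power from 81% to 65–46%. Both statements depend on assumed shares.

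A reader might infer that the primary result is biased, or biased toward the combination. The documents show neither. A reader might also conclude that the primary composite must be amended. That does not follow: power would fall to about 69% or 58% if 10% or 20% of otherwise successful patients in both arms exceeded the taper, the 54% v 23% basis would no longer apply, and an unmasked dosing decision would enter the endpoint directly.

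**What to change.** Leave the primary composite and its sample-size basis unchanged.

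1. Reconcile Study endpoints with Study treatments by stating how prednisolone above the taper is handled in the primary endpoint.
2. Prespecify, as the first supportive analysis of the primary endpoint, the same log-rank test with prednisolone above the protocol's existing week-28 and week-52 milestones counted as failure in either arm. The sponsor should set the tolerance before the analysis. No new dose rule is needed.
3. Require consistency between the two analyses before describing the result as a steroid-sparing benefit or as equal efficacy at lower steroid exposure.

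The cost is a short analysis-plan amendment and a little more analysis work. The supportive test may well have less power than the primary, as the table shows for equal taper-failure rates, so consistency should be judged on the direction and size of the effect and not on significance alone. Three secondary endpoints already need the prednisolone dose, but it must be confirmed that doses between visits are recorded.

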**Assessments**																						
SLEDAI/PGA	x		x	x	x	x	x	x	x	x	x		x	x	x	x	x	x	x	x	x	
SLICC damage score	x														x						x	
QoL questionnaire			x					x			x				x				x		x	
Treatment failure																					x	
Clinical and renal response											x										x	
Autoantibody reduction											x										x	
B cell depletion											x										x	
NET assay			x								x										x	

*S* screening, *B* baseline, *QoL* SF-36 quality of life questionnaire, *FU* follow-up, *SBLA* standard blood laboratory analysis, *Ig* immunoglobulins, *NET* neutrophil extracellular traps

^a^Baseline may be left out if planned within two weeks of screening. ^b^Kidney biopsy only in case of suspected renal involvement

Upon severe flares of SLE disease activity, alternative treatment options will be considered, which can result in the withdrawal of the subject from the study. Patients randomized to the standard-of-care treatment group can cross over to the intervention group in the case of either a severe flare or insufficient treatment response requiring a switch in medication. They will then be considered to have met the primary endpoint of treatment failure, will re-enter the study if they fulfill the inclusion criteria, and receive the complete study treatment of the intervention group as described above.

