### Statistical analysis

The statistical analysis will primarily be performed on the intention-to-treat population. For non-biased immunological endpoints, a per-protocol analysis will be done to assess the pathophysiological effects of adding belimumab and rituximab onto standard of care. The observed rates of treatment failure will be displayed in survival curves and the difference between treatment groups will be assessed using a log-rank test.

Differences in baseline characteristics, immunological endpoints, and clinical response will be explored. The absolute and percentage reduction of autoantibody titers, memory B cells, and NET formation will be analyzed as continuous variables using the non-parametric Mann-Whitney *U* test to compare treatment groups. Clinical disease activity categorized by the aforementioned response criteria will be analyzed using the chi-square test for dichotomized variables. Dosages of immunosuppressants will be analyzed as continuous variables using Mann-Whitney *U* because of the limited number of patients. Missing data will be imputed as that subject’s previously observed value. Patients that have crossed over from the control group to the intervention group will be considered as having met the primary endpoint of treatment failure and will re-enter the study as a new subject. As such, they will be included in the intention-to-treat analysis. Also, they will serve as their own controls in an additional post hoc analysis.

Safety, toxicity, and adverse events will be documented, and the events considered to be at least possibly related to the study treatment will be summarized by severity and treatment group. Infectious AE’s will be presented to an independent infectious disease specialist for evaluation of severity and relation to study participation.

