Monitoring will take place two times a year and the monitoring process will be independent from the investigators. Auditing visits will take place as deemed necessary by the auditing committee. Severe adverse events will be reported to the sponsor within 24 h. A data monitoring committee was not necessary based on the risks of the study. However, to ensure subject safety, safety meetings with independent specialists will be held four times a year in order to monitor and evaluate adverse events, treatment failures, and drop-out. A clinical trial insurance that provides coverage for damage to research subjects through harm caused by the study is available in accordance with the legal requirements in The Netherlands. When medically indicated, trial visits can be intensified as desired or supplemented with the trial’s independent physician in the case of adverse events or harm that occurred during the trial. Additional health care needs that arise during or as a consequence of the trial will be adequately addressed by the investigators.

Several methods are employed to improve participant retention and completion of follow-up, minimizing the burden and practical implications for patients. Scheduling of appointments is planned well ahead of time and reminders are included. Travel allowance will be provided for unplanned visits to the study center. Furthermore, patients who are withdrawn from the study medication will be followed at regularly scheduled study visits as specified by the protocol, unless informed consent is withdrawn. Treatment during the study is defined up to 104 weeks, after which the treatment with belimumab can be continued or patients can be switched to another immunosuppressive regimen as preferred by the treating physician in shared decision with the patient. In the Netherlands, belimumab is covered by insurance companies for the treatment of LN patients posing no barrier to continue any medication from either treatment arm in routine clinical practice after completion of the study.

Significant protocol amendments will be communicated with all relevant parties. We will submit our findings for peer-reviewed, open-access publication, and data resulted from this randomized clinical trial as well as other related documentation will be available on reasonable request. This paper complies with the Standard Protocol Items: Recommendations for Interventional Trials (SPIRIT) recommendations for protocol reporting [39].

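### Week-104 response comparisons can favour the intervention with no true effect, because rescued intervention patients can be scored after rescue while crossed-over controls appear to stay at the value that led to crossover

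*Protocol article*

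**What the plan says.** **Definitions (Study endpoints).** "Secondary clinical endpoints will be evaluated at 28 and 104 weeks". The first definition opens "Clinical response is defined as a reduction in SLEDAI of" at least 4 points, with PGA not worsening by more than 0.3. Remission adds a steroid limit. Renal response, low-level disease activity and disease control are likewise built from laboratory, SLEDAI, PGA and steroid values. None says what happens when the patient has already met treatment failure or been rescued.

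**Test and missing data (Statistical analysis).** "Clinical disease activity categorized by the aforementioned response criteria will be analyzed using the chi-square test for dichotomized variables". "Missing data will be imputed as that subject’s previously observed value".

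**Crossover (Study treatments, text after Table 2; Statistical analysis).** "Patients randomized to the standard-of-care treatment group can cross over to the intervention group in the case of either a severe flare", or when insufficient response calls for a change of medication. There is no such route for the intervention arm. Re-entry is conditional: such patients "will re-enter the study if they fulfill the inclusion criteria". In the analysis they "will be considered as having met the primary endpoint of treatment failure and will re-enter the study as a new subject", and the article adds that they are part of the intention-to-treat analysis.

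**Follow-up after stopping (Ethical considerations and dissemination).** Unless consent is withdrawn, "patients who are withdrawn from the study medication will be followed at regularly scheduled study visits as specified by the protocol". The text after Table 2 also says that a severe flare may end in withdrawal from the study itself.

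**The concern.** Take two patients with the same invented course: baseline SLEDAI 16, a major flare to 18 at week 40, then recovery after rescue to 4 on 5 mg prednisolone at week 104, with PGA not worse.

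- The intervention patient comes off study medication but keeps the scheduled visits. The week-104 value is observed and is 12 points below baseline: a responder, and in remission at 5 mg, although a primary treatment failure.
- The control crosses over and becomes a separate subject. The original record has no later values of its own, so the carry-forward rule leaves it at 18, which is 2 points above baseline: a non-responder.

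Recovery after rescue is credited in one arm and not in the other. Such a comparison estimates neither the effect of assignment whatever treatment follows, nor the effect of the two strategies without rescue. Every dichotomous week-104 response endpoint is exposed. The intervention patient's value is observed, so a different imputation rule for missing values would not by itself remove the problem.

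**Working it through.** The article gives no figure for these endpoints, so there is none to reproduce. Its planning rates serve only to set the failure risk. They are consistent with its hazard ratio: ln(1 − 0.54)/ln(1 − 0.23) = 2.97.

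**Inputs from the article:** 35 patients per arm; 54% failure planned in the control arm and 23% in the intervention arm (mean 38.5%); a 5% level, taken as two-sided.

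**Assumed inputs, not in the article:**
- failure risk f = 0.40 or 0.54, the same in both arms (no effect);
- week-104 response without failure, 0.90;
- share of failures that are flare or non-response, s = 0.50 to 0.70, with all such controls crossing over;
- recovery after rescue, r = 0.30 to 0.67;
- share w of the corresponding intervention patients who stay in follow-up;
- carried-forward values score as non-response; the remaining failures have response r in both arms.

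**Formulas**
- Control: (1 − f) × 0.90 + f(1 − s)r
- Intervention: the same plus f·s·w·r
- Spurious difference: f·s·w·r

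**Example.** f = 0.40, s = 0.50, r = 0.50, w = 1. Control 0.54 + 0.10 = 64%; intervention 0.54 + 0.10 + 0.10 = 74%; difference 10 points.

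**Results.** Rejection rates come from exact enumeration of the uncorrected chi-square test, 35 per arm.

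| f | s | r | Difference, w = 1 | Type I error, w = 1 | Difference, w = 0.5 | Type I error, w = 0.5 |
|---|---|---|---|---|---|---|
| 0.40 | 0.50 | 0.30 | 6.0 | 8.2% | 3.0 | 5.7% |
| 0.40 | 0.50 | 0.50 | 10.0 | 14.9% | 5.0 | 7.5% |
| 0.40 | 0.70 | 0.67 | 18.8 | 41.4% | 9.4 | 13.5% |
| 0.54 | 0.50 | 0.30 | 8.1 | 9.3% | 4.1 | 5.5% |
| 0.54 | 0.70 | 0.50 | 18.9 | 35.4% | 9.5 | 11.3% |
| 0.54 | 0.70 | 0.67 | 25.3 | 61.9% | 12.7 | 18.1% |

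With w = 0 the difference is zero and the rejection rate is 4.3% to 5.2%.

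**Two further conditions.** If only a share c of the eligible controls cross over, and a carried-forward value is a response with probability h, the difference becomes f·s·c·w·(r − h). In the example above, c = 1 and h = 0.20 give 0.40 × 0.50 × 0.30 = 6 points and 8.5% rejection. With h = r the difference vanishes.

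**Cross-check with a second model** (f = 0.385, 80% response without failure, 50% recovery). Half crossing over and half followed: 0.385 × 0.5 × 0.5 × 0.5 = 4.8 points, 6.3% rejection. Full crossover and full follow-up: 19.3 points, 36.5%. In that last case, adding the re-entered records to the intervention arm leaves the mean difference unchanged and raises rejection to about 44%.

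**With the fix.** If earlier flare or non-response counts as non-response in both arms, both response rates equal the control formula above. The difference is zero and the rejection rate is 4.3% to 5.2%. Scoring every failure as non-response gives 4.4% to 4.7%.

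**The case against.** - **Flaring intervention patients may leave the study.** The text after Table 2 allows this, and the list of prohibited drugs limits what rescue can be given within the study. A patient who leaves is carried forward just as the control is. This stands as a condition, and it decides the size. It does not remove the point: withdrawal is stated as possible, not as the rule, the primary endpoint lists it separately from flare and non-response, and follow-up off study medication is promised.
- **Freezing of the control record is inferred.** No sentence says that the original record ends at crossover. This stands; but once the person is a separate subject, the article names no other source for that record's week-104 value.
- **A frozen value need not be a non-response.** A control who falls from 16 to 4 and flares to 12 is still 4 points below baseline and may count as a responder. This stands and shrinks the gap for clinical response.
- **The inputs are assumed and the largest figures are corner values.** This stands. Crossover is also optional and conditional on the inclusion criteria.
- **Scoring visit status whatever came before is a legitimate choice, often detailed in an analysis plan.** True, if applied alike in both arms. Here the article itself fixes rules on re-entry, carry-forward and follow-up that together treat the arms differently.
- **The endpoints are secondary and described as explored.** This stands and limits the consequence.

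**Conclusion.** The point holds in conditional form. Following the article as written can score the same clinical course differently by arm, in the intervention's favour whenever rescue yields a response more often than the carried-forward value does. Under the assumed inputs, the spurious gain is 6 to 25 points with type I error of 8% to 62% if all rescued intervention patients stay. It is about 3 to 13 points and 5.5% to 18% if half leave, and zero if all leave.

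A reader might infer that the bias is certain, or that 62% estimates the error rate of this trial. The documents support neither: they do not say how many failing intervention patients remain, how many controls cross over, or how often rescue succeeds. Nor is the primary result touched by this, since flare, non-response and crossover already count as treatment failure in the log-rank comparison. The change is worth making because the affected endpoints are the main clinical secondary ones, the trial is open-label, and the remedy is cheap.

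**What to change.** Add to the response definitions, for example: *A randomised patient who has met a disease-related component of treatment failure before the assessment (flare, non-response, re-induction, plasmapheresis, end-stage renal disease, death) is a non-responder for all response, remission, low-activity and disease-control endpoints at that assessment and later, in both arms.*

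In addition:
- Count a crossover through the flare or insufficient response that triggered it, and apply the same scoring criterion to intervention patients. Listing crossover itself would leave a route to non-response open to controls only.
- Compare randomised subjects only, and keep re-entered records out of this comparison.
- As a sensitivity analysis, report the observed week-104 status of all randomised patients under their original arm, crossovers included.
- Reconcile the text after Table 2, Statistical analysis, and Ethical considerations and dissemination on who is followed after failure.

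Cost: a few sentences. The main analysis needs no new data; the sensitivity analysis only requires crossover visits to be linked to the original randomisation. Downsides: week-104 response rates fall, late responders after an early non-response are not credited, and these endpoints move closer to the primary.
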